### Recruitment

The goal is to recruit approximately 13 participants from each participating unit. Participants will be recruited by treating OTs or special education teachers from patient rosters in the units. The eligibility assessment, including administration of the WCPA-SE, will be done by the recruiting staff. If the person is found eligible, oral and written information will be given about the trial, including the two possible interventions and the randomisation process. If they agree to participate, a consent form will be signed by the participant.

## Methods: assignment of interventions

### Allocation (randomisation)

#### Sequence generation

The randomised allocation will be performed by using a computer-generated numbering sequence which will be carried out by a professional academic statistician. The basic requirement is a ratio of 1:1. A multiple varying block randomisation stratified by centre will be performed. The reason for this strategy is to allow for differing numbers of recruited participants from different centres.

#### Allocation concealment mechanism

The allocation sequence and block randomisation strategy will be concealed from the staff recruiting the participants. Each interventionist will be given a personal code and will assign the recruited participant a unique participant number consisting of the interventionist’s personal code with an added serial number. For each new participant, the recruiting staff will contact the trial coordinator via telephone or e-mail, who will reveal the allocated intervention for the specific participant.

#### Blinding (masking)

Blinding to intervention allocation of interventionists or participants will not be possible in this trial. The interventionists conducting TAU will however be blinded to baseline assessment results and the statistician will be blinded to group allocation.

## Methods: data collection, management, and analysis

### Data collection methods

Data for participants in the LGO-S intervention will be collected by trained group leaders who will be local OTs working at the participating clinics. Along with the mentioned training workshop in the LGO-S intervention, all group leaders will also be trained in administering the measures used in this trial. During training, the group leaders will be instructed to ensure that data is complete at the time of data collection while being with the participant. As stated above, data for participants in the TAU intervention will be collected by the research group. For each participant, the same data collector will collect all data in order to avoid inter-rater bias, as far as practically possible.

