### Data management

To manage the data, a web-based system called Smart-Trail (S-T) will be used. S-T is a secure system and the content is tailored for this trial with web-based forms for each data collection point. There is automatic marking for the event that data are missing or entered inaccurately. Each participant can be efficiently followed throughout the trial, and the data are organised by unit. The system thus gives a clear visual overview of each participant’s status. The use of S-T fulfils the requirements of the European General Data Protection Regulation (GDPR). Only parts of the research group will have access to S-T. To gain access to the system, the principal investigator has to approve of this action, and also decide what role the researcher who is gaining access will have (i.e. entering or viewing data). The S-T has a two-step login function and each login is tracked by the system.

Directly after randomisation, the participant will be registered in S-T with their participant code and intervention allocation. Raw data will then be collected on paper forms, one bundle for each data collection point containing all measures applicable to the specific occasion. The forms in the bundles are in their original formats and have not been changed by the research group. Forms will be marked with the participant’s code and entered manually by the researchers. When the data collection is finished and all raw data are entered into S-T, the data will be exported to statistical software for further analyses.

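### Outcomes are collected by LGO-S group leaders in one arm and by the research group in the other, apparently from a baseline taken after allocation is known, so collector type cannot be separated from treatment

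*Protocol article*

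**What the plan says.** **Who collects.** The section Data collection methods has one rule for each arm. For LGO-S: "Data for participants in the LGO-S intervention will be collected by trained group leaders who will be local OTs working at the participating clinics". For TAU: "As stated above, data for participants in the TAU intervention will be collected by the research group"; the article contains no earlier statement to which this refers. On completeness, "the group leaders will be instructed to ensure that data is complete at the time of data collection while being with the participant". The section adds: "For each participant, the same data collector will collect all data in order to avoid inter-rater bias, as far as practically possible". Data monitoring confirms that some staff both deliver the intervention and collect data.

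**When allocation is known.** Under Allocation concealment mechanism, recruiting staff contact the trial coordinator for each new participant, "who will reveal the allocated intervention for the specific participant". Data management gives the order: "Directly after randomisation, the participant will be registered in S-T with their participant code and intervention allocation". The next sentence is: "Raw data will then be collected on paper forms, one bundle for each data collection point containing all measures applicable to the specific occasion".

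**What is blinded.** Under Blinding, neither participants nor interventionists are blinded. TAU interventionists are kept unaware of baseline results, and the statistician is unaware of the arm. No matching restriction is stated for LGO-S group leaders, who collect the data in their arm.

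**What is acknowledged.** The Discussion lists unblinded assessors as a limitation and argues that assessor bias is secondary because most outcomes are self-reported. It does not say that a different kind of assessor is used in each arm.

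**The concern.** The primary comparison is the between-arm difference in change on the ATMS-S time management subscale. The plan has two features that could feed into that difference without any effect of the course.

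First, after ten weeks, LGO-S participants hand in ratings of the skills they were taught to staff who lead the course. TAU participants hand theirs to researchers who did not treat them. Keeping one collector per participant controls variation within a person but leaves the contrast between arms untouched.

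Second, if people already know their arm at baseline, the baseline rating itself may move with that knowledge, and it enters the change score directly.

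ATMS-S is self-administered, so the threat there is to how participants respond. SDO-OB is interview-based, and in WCPA-SE the test leader notes the strategies used. For these two the collector takes part in producing the score. At stake is whether a positive result can be attributed to LGO-S rather than to how the data were gathered.

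**Working it through.** **1. Is collector type separable from arm?** LGO-S goes with group leaders and TAU with the research group; no third combination is described. An indicator for collector type would equal the indicator for arm. The t-test or Mann–Whitney test has no such term. The sensitivity regression for clustering by centre cannot estimate one, because the alignment holds within every centre. Blinding the statistician does not alter it.

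**2. Does baseline follow disclosure?** Three statements point the same way:
- the coordinator reveals the arm for each new participant at recruitment;
- registration with the allocation comes directly after randomisation, and raw data for each collection point come after that;
- the collector is chosen by arm and, as far as practicable, stays the same throughout, so the arm must be known when baseline is collected.

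Only the WCPA-SE done for eligibility clearly comes earlier, and the plan uses the second WCPA-SE as baseline. This is an inference: Table 2 and Fig. 1 are not shown.

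**3. What cancels and what does not?** Let s be the part of a score due to collector or setting. Then

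observed difference in change = true effect + (s_LGO,post − s_LGO,base) − (s_TAU,post − s_TAU,base).

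If s is constant over time within each arm, both brackets are zero and nothing is added. If s changes over time differently in the two arms, the net shift b is added in full.

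**4. The plan's own figure.** Sample size section: difference 8, SD 10, power 80%, level 0.01 (taken as two-sided), dropout 25%. The noncentral t calculation gives 39 per arm (power 81.0%). Then 39 / (1 − 0.25) = 52 per arm, or 104 in total, as stated. So 39 completers per arm is the planned analysis size.

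**5. Illustration.** SE = 10 × √(2/39) = 2.26 units. With no true effect, the rejection probability is that of a two-sided t-test on 76 degrees of freedom with noncentrality b / 2.26. The analysis section sets the 5% level.

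| Assumed net shift b (units) | b / SE | False positives, 39 per arm | False positives, 52 per arm |
|---|---|---|---|
| 0 | 0 | 5.0% | 5.0% |
| 1 | 0.44 | 7.2% | 8.0% |
| 2 | 0.88 | 14.1% | 17.3% |
| 3 | 1.32 | 25.8% | 32.9% |
| 4 | 1.77 | 41.5% | 52.4% |

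At the 1% level used for the sample size, 39 per arm gives 1.7%, 4.4%, 10.0% and 19.8% for shifts of 1 to 4 units. Every value of b is assumed.

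**6. How much can still be changed?** Trial status reports 75 of 104 recruited on 9 April 2021, so at most 104 − 75 = 29 remain. After 25% dropout, 29 × 0.75 ≈ 22, or about 11 per arm. SE = 10 × √(2/11) = 4.26, and the 95% half-width is 2.086 × 4.26 ≈ 8.9 units. That exceeds the planned 8-unit effect, so comparing results by collection route could not detect a shift of 1 to 4 units.

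**The case against.** The best counter-argument is that the primary outcome is a self-administered form analysed as change from baseline, with the same collector throughout. Any stable collector offset then disappears. This stands, and it limits the point to shifts that vary over time. In addition, unblinded participants can show response bias whoever collects the form, so the extra part due to the collector is unknown. The Discussion also describes a response shift that would make the effect look smaller, so the direction is not settled.

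A reader might infer that each participant's own group leader watches as the items are rated. The text does not say so. It says that group leaders collect the data and ensure completeness while with the participant. Nor does it state outright that baseline follows disclosure, although the inference is strong.

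The protocol already admits unblinded assessors, but that does not answer the point. Its reassurance is that response shift could occur in both arms, and collection that differs by arm weakens that symmetry.

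**Conclusion.** The point holds as a structural weakness. Collector type is fully aligned with arm, no planned analysis can undo this, and baseline very probably follows knowledge of the allocation. Exposure is most direct for SDO-OB and WCPA-SE and less direct for ATMS-S.

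The size of any bias is unknown. The false-positive rates of about 7% to 41% assume net shifts of 1 to 4 units, 39 completers per arm, SD 10, a two-sided 5% test and no true effect. They show sensitivity and do not estimate the bias in this trial.

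Two stronger readings are tempting but unsupported. One is that the primary result is known to be biased in favour of LGO-S; the documents establish neither direction nor amount. The other is that recording the collection route would rescue the data already gathered. In those data route equals arm, so a flag only describes the problem.

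**What to change.** **Participants not yet randomised**
1. The coordinator reveals the allocation only after the complete baseline bundle has been received.
2. Self-report forms, ATMS-S first, follow one route in both arms: completed alone, returned sealed to the research group, and checked for completeness at data entry.
3. Where existing staffing allows, the same type of non-treating collector handles SDO-OB and WCPA-SE in both arms. The documents give no collector numbers per unit, so this cannot be assumed feasible everywhere.

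**Participants already enrolled**

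Do not switch collector or route midway. That would break the same-collector rule and could stop a constant offset from cancelling. State the arm-specific collection and the timing of baseline relative to allocation as a limitation in the trial report. A route flag may be kept for description only.

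**Cost**

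Items 1 and 2 need a revised work instruction, envelopes and a later randomisation call, which has to fit the 1–2 weeks between baseline and the start of the intervention. They need no extra staff; item 3 may need collector time rearranged. The main drawback is a change of procedure late in recruitment that reaches at most about 29 of the 104 participants, and fewer if recruitment has moved on since April 2021.

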### Data management

To manage the data, a web-based system called Smart-Trail (S-T) will be used. S-T is a secure system and the content is tailored for this trial with web-based forms for each data collection point. There is automatic marking for the event that data are missing or entered inaccurately. Each participant can be efficiently followed throughout the trial, and the data are organised by unit. The system thus gives a clear visual overview of each participant’s status. The use of S-T fulfils the requirements of the European General Data Protection Regulation (GDPR). Only parts of the research group will have access to S-T. To gain access to the system, the principal investigator has to approve of this action, and also decide what role the researcher who is gaining access will have (i.e. entering or viewing data). The S-T has a two-step login function and each login is tracked by the system.

Directly after randomisation, the participant will be registered in S-T with their participant code and intervention allocation. Raw data will then be collected on paper forms, one bundle for each data collection point containing all measures applicable to the specific occasion. The forms in the bundles are in their original formats and have not been changed by the research group. Forms will be marked with the participant’s code and entered manually by the researchers. When the data collection is finished and all raw data are entered into S-T, the data will be exported to statistical software for further analyses.

### Statistical analysis plan

#### General statistical considerations

The flow of participants through the study will be illustrated according to the Consolidation Standard of Reporting Trials (CONSORT, Fig. 1) [78].

Prior to data analysis, raw data from each instrument will be coded according to the instructions for the respective instrument. Statistical tests will be two-sided and conducted at the conventional (two-sided) 5% level with no formal adjustment for multiple testing. Secondary outcomes are likely to be highly correlated so that standard adjustment techniques, such as the Bonferroni method, would be conservative [79].

All outcome measures and patient characteristics will be summarised by their trial allocation group and by measurement point. The distribution of outcome data will be examined. The main analysis of outcome data will be the comparison of change from baseline between treatment arms. Change from baseline has a “normalising” effect and standard techniques are generally applicable. To maintain the baseline comparability of the compared groups, the main analyses will be performed on an intention-to-treat basis, meaning that participants will be analysed in the arm they were allocated to. A researcher blinded to group allocation will conduct the statistical analysis, guided by a professional academic statistician (also blinded).

#### Analysis of baseline data

Baseline demographic and clinical characteristics will be reported for each treatment arm using descriptive statistics (mean and SD or median and IQR for continuous variables, and absolute number and percentage for categorical variables). Normality will be assessed graphically and with the Shapiro–Wilk test.

#### Primary outcome analysis

The pre-specified primary endpoint in this trial is the change from baseline in time management skills as measured with the ATMS-S immediately after the intervention compared between the LGO-S and TAU treatment arms. Differences will be analysed with an independent *t*-test or the Mann–Whitney *U*-test, depending on the distribution.

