#### Handling of missing data

Missing data may compromise findings from randomised clinical trials, particularly if missingness is not at random (MAR) and if missing data are not handled appropriately [80]. We will follow recommendations in the paper by Jakobsen et al. to handle missing data. This may include best-worst and worst-best sensitivity analyses, and full information maximum likelihood [80]. In the case of single missing observations on the three subscales of ATMS-S, person measures (subscale units per person) will be calculated using anchored item difficulty and category structure in a Rasch analysis. Winsteps software (updated version) will be used for Rasch analyses.

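### The primary test is an unadjusted t-test or Mann–Whitney test on change scores, picked without a stated rule: the estimand is not fixed and precision is given up

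*Protocol article*

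**What the plan says.** The Primary outcome analysis section fixes the endpoint: "The pre-specified primary endpoint in this trial is the change from baseline in time management skills as measured with the ATMS-S", compared between arms immediately after the intervention. It then gives the test: "Differences will be analysed with an independent *t*-test or the Mann–Whitney *U*-test, depending on the distribution". The Secondary outcome analysis section applies the same procedure to the secondary outcomes.

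On the choice between the two tests, General statistical considerations says "The distribution of outcome data will be examined" and justifies change scores with "Change from baseline has a “normalising” effect and standard techniques are generally applicable". A normality check is named only under Analysis of baseline data, with no cut-off: "Normality will be assessed graphically and with the Shapiro–Wilk test". The outcome description of the ATMS-S leaves open whether means or medians will be analysed.

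On design, Sequence generation says "A multiple varying block randomisation stratified by centre will be performed", and the trial runs in ten units. Centre does not appear in the primary test. The Sensitivity analyses section adds a regression that allows for correlation within centres.

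On the analysis set, the main analyses are labelled intention-to-treat, defined only as analysis in the allocated arm. On missing data the article follows published recommendations: "This may include best-worst and worst-best sensitivity analyses, and full information maximum likelihood". It also gives a Rasch method for single missing ATMS-S items.

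**The concern.** There are three linked problems, all in what the article states.

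1. **The estimand is open.** A t-test compares mean changes; a Mann–Whitney test compares ranks. The sample size rests on a difference in means, and the planned cost-effectiveness analysis on the ATMS-S needs a difference in effects. If the data lead to the rank test, the primary result no longer matches either.
2. **Available information is not used.** Baseline enters only by subtraction, which fixes its coefficient at 1. Where the baseline–post correlation is below 1, this gives a noisier estimate than covariate adjustment and leaves part of any chance baseline imbalance in the contrast. Centre was used to stratify randomisation but is absent from the primary test. The article says the centre-adjusted regression is there to obtain a sound effect estimate and standard error, yet gives it only sensitivity status.
3. **The analysis set is not tied to the test.** A two-sample test on observed changes has no place for someone without a post-intervention score, and the missing-data methods are optional and not linked to it.

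At stake are the precision and interpretability of the primary result, more than its false-positive rate.

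**Working it through.** **Inputs from the article.** Sample size section: difference 8, SD 10, 80% power, 25% dropout, significance level 0.01, 52 per arm. General statistical considerations: two-sided 5% tests. ATMS-S description: subscale test–retest ICC 0.82–0.86. The baseline–post correlation r is not given, so a range is assumed. The ICC is a loose upper guide, since an intervention period may lower the correlation.

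**Reproducing the plan's figure.** Standardised difference 8/10 = 0.8. A two-sample t-test at two-sided 0.01 with 80% power needs 38.2, so 39 per arm; 39/0.75 = 52 per arm, 104 in total. This matches exactly. The size therefore expects 26 of 104 without a post-intervention score and 78 (39 per arm) with one.

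**Baseline adjustment.** With equal variance s² at both times, the change score has variance 2(1−r)s² and the ANCOVA residual (1−r²)s². The ratio is (1+r)/2. Take 10 as the SD of change; the residual SD is then 10·√((1+r)/2), and power comes from the noncentral t distribution with 39 per arm.

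| Analysis | Variance ratio | SD | N per arm with dropout (difference 8, α 0.01) | Power, difference 5, α 0.05 | Power, difference 8, α 0.05 |
|---|---|---|---|---|---|
| Change score | 1 | 10 | 52 | 59% | 94% |
| ANCOVA, r = 0.5 | 0.75 | 8.66 | 40 | 71% | 98% |
| ANCOVA, r = 0.7 | 0.85 | 9.22 | 44 | 66% | 97% |
| ANCOVA, r = 0.86 | 0.93 | 9.64 | 48 | 62% | 95% |

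At r = 0.82 the ratio is 0.91. The article does not say whether 10 is the SD of change or of scores. The ratio is the same either way. The power columns are not: if 10 is the SD of scores, the SD of change is 10·√(2(1−r)), which is 10 at r = 0.5 and 5.3 at r = 0.86, so unadjusted power would be higher at the larger correlations.

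**Chance imbalance.** Assume a score SD of 10. The SE of the baseline difference is 10·√(2/52) = 1.96 for all randomised, or 10·√(2/39) = 2.26 among 39 completers per arm. Given an imbalance of 3 units (about 1.5 or 1.3 SE), the change-score contrast shifts by (1−r)×3: 1.5 units at r = 0.5, 0.9 at 0.7, and 0.54 to 0.42 at 0.82 to 0.86. Averaged over randomisations, the contrast is unbiased.

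**Centre.** If arms are balanced within centre and centres explain a share f of the variance, the true SE divided by the t-test SE is √(1−f). For assumed f of 1%, 5% and 10%, the real two-sided level of a nominal 5% test is 0.049, 0.044 and 0.039. Omitting centre is conservative. This covers centre effects common to both arms; it does not address correlation within LGO-S groups.

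**Choosing the test from the data.** The rule had to be assumed: Shapiro–Wilk at 0.05 in each arm, t-test if both pass, otherwise Mann–Whitney. With 39 per arm and 4,000 simulated trials per setting, type I error at the 5% level was 0.048 (normal), 0.043 (t with 4 degrees of freedom) and 0.054 (exponential).

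**The case against.** A change-score contrast is valid in a randomised trial, and much of what a reader might infer from this section goes too far.

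- **That baseline is thrown away.** It is not; it is subtracted. What is missing is covariate adjustment.
- **That the plan ignores centre.** It does not. The sensitivity regression allows for centre, and leaving centre out of the primary test makes that test conservative.
- **That everyone without a post-intervention score is dropped.** No section says so. The missing-data section allows for full information maximum likelihood and best-worst analyses, and the sensitivity section looks at those lost to follow-up. What stands is that these methods are optional and not connected to the primary test.
- **That choosing the test from the data inflates false positives or lets the result be steered.** The analyst and the statistician are blinded to allocation, which limits steering, and the simulated type I error stays close to 5%. A cut-off for the normality check could also sit in a fuller analysis plan that is not shown.
- **That adjustment is worth a third more participants.** That is 1/0.75 = 1.33, and it holds only at an assumed r of 0.5. Near the ICC the gain in variance is 7–9%. For the 8-unit target at the 5% level, power is adequate without adjustment.

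The central criticism stands: the article's own analysis section names two primary tests with different estimands, gives no rule for choosing between them, and adjusts for neither baseline nor the stratification factor. That is stated text, not a detail left elsewhere.

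**Conclusion.** The point holds as one of pre-specification and efficiency. The primary estimand is not fixed, and baseline and centre are not adjusted for in the primary test. Baseline adjustment would lower the variance by 25% at an assumed r of 0.5, 15% at 0.7 and 7–9% at 0.82–0.86, assuming equal variances at the two times. The benefit lies mainly in effects below the planning value: the gain at 5 units is about 3 to 12 percentage points of power, taking 10 as the SD of change, whereas at 8 units there is little left to gain. The calculation ignores the few degrees of freedom spent on covariates and counts no gain from centre. Type I error is not the problem. Nor can it be said that participants without a post-intervention score are excluded; the article simply does not fix how they enter the analysis it calls intention-to-treat. The change is worth making because it settles the estimand and improves precision with data already being collected.

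**What to change.** Pre-specify one primary analysis before allocation is revealed to the analyst:

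- A linear model (ANCOVA) for post-intervention ATMS-S time management with arm, baseline ATMS-S and centre, or the equivalent likelihood-based mixed model that also uses the 3-month value. Name which of the two it is.
- Participants are analysed in their allocated arm under a stated missing-at-random assumption. The mixed model has the advantage of using those who miss the post-intervention visit but attend at 3 months.
- The adjusted mean difference at the post-intervention visit is the primary contrast.
- Mann–Whitney becomes a labelled sensitivity analysis. The best-worst and worst-best analyses become committed sensitivity analyses for participants with no post-baseline value, whom neither model recovers.
- The same model serves the continuous secondary outcomes.

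The cost is revised analysis wording and slightly more analysis work. No new data are needed.
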